### 5.2 Exclusion Criteria

#### *Exclusion criteria related to the ERP*

- OCD symptoms primarily associated with hoarding
- Ongoing substance abuse/dependence
- Bipolar disorder or psychosis
- Ongoing/ planned suicidal ideation
- Mental Retardation, based on previous medical history
- If using antidepressants:
  - Not on stable dosage 12 weeks before the intervention
  - Unwilling to remain on stable dosage during the four intervention days

- Unwilling to refrain from anxiety reducing substances, such as anxiolytics (e.g. benzodiazepines) and alcohol during the two days of exposure.
- Patients living > 1 hour drive by car/ train from the treatment location.

#### ***Additional exclusion criteria related to the DCS***

- Pregnancy or breast feeding (the participants are informed that they will have to use contraception the two days when the DCS/placebo is administered. Females will be asked if they are pregnant, and in case of doubt a pregnancy test is provided)
- Renal impairment
- Hypersensitivity to D-Cycloserine
- Porphyria
- Epilepsy

According to the SPC, depression and anxiety should also be exclusion criteria for the administration of DCS. However, in the current study DCS will be administrated in a low dosage for two consecutive days. Several studies have used DCS in the treatment of OCD with the same kind of exclusion criteria, and reported no adverse side effects [8, 9, 62], and studies of other anxiety conditions show the same results [6, 64].

### **5.3 Withdrawal**

#### ***Criteria for mandatory discontinuation of treatment, including DCS administration:***

- Consent withdrawal by the patient
- High suicide risk according to investigator's judgment or any suicide attempts during the two days administration of the DCS. These patients will be excluded from the study, and taken care of according to the normal procedures of specialist health care in Norway.
- Worsening of OCD symptoms during the two days of DCS-administration, which in the opinion of the investigator requires an adaptation of treatment not compatible with the protocol or requires hospitalization.

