### 11.2 Treatment Assignment/ Randomization

Patients are upon inclusion randomly assigned to DCS or placebo using a 2:2:1 ratio of 250 mg DCS: 100 mg DCS: placebo. In order to control for potential interaction effects with antidepressants (121), patients will be stratified on current anti-depressive medication or not. Within each subgroup patients will be randomized in blocks of 5 into ERP+DCS 100 mg, ERP+DCS 250 mg, or ERP + Placebo in the proportions 2:2:1.

A research unit at Karolinska Institute, Sweden, which is not involved in the study, will be responsible for the randomization. Randomization lists will be sent directly to Kragerø pharmacy that will be responsible for providing the medication for patients enrolled.

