### **11.7 Continuation of cET-Treatment in discontinuation of DCS-treatment**

If a participant decides not to take the DCS/placebo treatment Day 2, he/she has still the opportunity to continue the concentrated ERP treatment, but the patient will be excluded from the study. The whole trial will end when the last subject has completed the 12-month follow-up telephone assessment (separate papers describing the short- and long-term effects of DCS will be written). A 5 year follow-up telephone assessment will be conducted and data will be collected and analyzed separately.

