## 13. Statistics and Data Management

### 13.1 Statistical Analysis

Statistical analysis will be performed by the investigator and specially designated collaborators and quality controlled and cross-checked by independent party

The primary objective is to demonstrate superiority of concentrated ERP + DCS vs. concentrated ERP + placebo at significance level of  $< 0.05$  (5%). Data will basically be analyzed using intention to treat methodology with a mixed models design, accounting for missing data, with relevant covariates for a given analysis. Data will primarily be analyzed employing multivariate methods (ANOVAs/MANOVAs) with repeated measurement.

Covariates are described in the moderator section (Chapter 6.5). Missing data will be replaced (multiple imputation methods). There will be calculations of effect sizes (Cohen's effect size) for all primary and secondary endpoints. Other relevant multivariate statistical analyses will be performed if relevant to elucidate results of importance to the objectives of the study. Safety data (e.g. side effects) will be collected and summarized in the study results.

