### 13.2 Determination of Sample Size

A meta-analysis by Norberg, Krystal & Tolin [69] found a medium effect size for ERP + DCS for heterogeneous samples of OCD-patients. However, in the current study, only patients who have relapsed after an initially successful ERP-treatment will be included. This is a sample which supposedly increases the possibility to detect DCS-effects and we assume that the effect size would be larger than that found in previous studies. In order to have 80% power to detect a moderate effect size ( $d = 0.50$ ) at an alpha-level of 0.05 a total of 160 patients will be included (64 in each of the DCS-conditions and 32 in the Placebo group). Patients lost or withdrawing from the study will be treated as drop-outs and replaced. We estimate an increased sample size of 10 patients, in total, to compensate for possible drop-outs.

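### Exclusion and replacement of randomised patients (Sections 5.3, 11.7 and 13.2) conflict with the intention-to-treat analysis stated in Section 13.1

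*Protocol*

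**What the plan says.** **Randomisation and analysis.** Section 11.2: "Patients are upon inclusion randomly assigned to DCS or placebo using a 2:2:1 ratio". Section 13.1: "Data will basically be analyzed using intention to treat methodology with a mixed models design, accounting for missing data". It adds: "Missing data will be replaced (multiple imputation methods".

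**Rules that act after randomisation.**
- Section 5.3, on high suicide risk or a suicide attempt during the two dosing days: "These patients will be excluded from the study, and taken care of according to the normal procedures".
- Section 11.7, on a patient who declines the Day 2 capsule: concentrated ERP may continue, "but the patient will be excluded from the study".
- Section 13.2: "Patients lost or withdrawing from the study will be treated as drop-outs and replaced". The next sentence there allows 10 extra patients in total for drop-out. Section 5 sets 160 as the maximum.

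**Text that points towards retention.** After treatment is discontinued for any reason between T0 and T2, Section 5.4 asks for an early end-of-study visit with the follow-up assessments. Section 11.8 keeps patients who worsen and contact the OCD team. Section 12.8 follows adverse events until they resolve. In Section 5.3, worsening of OCD on the dosing days stops treatment, but exclusion is not mentioned. The same holds for serious adverse events.

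**The concern.** Intention to treat means that every randomised patient counts in the assigned arm. Patients are randomised at inclusion, so all three rules remove or substitute people who already have an arm. The protocol cannot follow these rules and also analyse everyone who was randomised.

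Two things are at stake. The first is the comparison itself. High suicide risk or an attempt on a dosing day can be related to outcome or to the drug, so removing those patients can be informative. Declining the Day 2 capsule is different: it comes before any dose and is blind to arm, so it mainly breaks the definition of the analysis set. The second is data that will not exist. The hypothesis in Section 3 places the DCS advantage at follow-up. A patient excluded on Day 2 or 3 has no 3- or 12-month Y-BOCS, and one early end-of-study visit does not supply it. A later analysis plan can define a set, but it cannot recover outcomes that were never collected.

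**Working it through.** **1. The plan's own figures.** Section 13.2 gives 64 + 64 + 32 = 160 patients, d = 0.50, alpha 0.05 and 80% power. With SD = 1, the noncentrality is d × √(n1·n2/(n1+n2)).
- Pooled DCS against placebo, 128 v 32: 0.50 × √25.6 = 2.530.
- One-sided: Φ(2.530 − 1.645) = 81.2%. Two-sided: Φ(2.530 − 1.960) = 71.6%.

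For this contrast the stated 80% is reproduced one-sided. The protocol does not state sidedness; that is a separate matter, and this point does not depend on it. The drop-out allowance is 10 of 160 + 10 = 170, or 5.9%.

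**2. The rules side by side.**

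| Group | Rule | Timing | Can it depend on drug or outcome? |
|---|---|---|---|
| High suicide risk or attempt | Excluded (5.3) | During the two dosing days | Yes |
| Declines Day 2 capsule | Excluded (11.7) | Before the first dose | Unlikely to depend on arm |
| Lost or withdrawn | Replaced (13.2) | No time stated | Possibly |

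All three fall after randomisation. Section 5.4 adds one early visit after treatment discontinuation but does not secure T2 and T3. Mixed models and multiple imputation can use a patient with partial data only if that patient stays in the analysis set, which the protocol does not say.

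**3. Size of a possible bias.** Let a share f of an arm be removed, with these patients k SD worse than the rest. The full-arm mean is then f·k below the mean of the rest, so removal improves the arm by f·k. The bias in d in favour of DCS is k × (f_DCS − f_placebo).

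Assumptions, none of them in the protocol: removed patients leave the analysis, replacements resemble the remaining patients and restore 128 v 32, and k is 1 to 2.

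*10 removed (the full allowance)*
- Following the 4:1 allocation: 8/136 = 5.9% and 2/34 = 5.9%; bias 0.
- All from DCS: 10/138 = 7.2%; bias +0.07 to +0.14.
- All from placebo: 10/42 = 23.8%; bias −0.24 to −0.48.

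*5 removed*
- Following the allocation: bias 0.
- All from DCS: 5/133 = 3.8%; bias +0.04 to +0.08.
- All from placebo: 5/37 = 13.5%; bias −0.14 to −0.27.

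The yardstick is the design effect of 0.50. The placebo arm is the more sensitive because it has only 32 patients.

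**4. After the fix.** With no replacement and all randomised patients analysed, the set is 160, or 170 if the 10 extra are enrolled up front. At 170 (136 v 34) the noncentrality is 0.50 × √27.2 = 2.608. For the same d, power is then 83.2% one-sided and 74.1% two-sided. The fix needs no larger sample.

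**The case against.** A reader might infer that the trial becomes a completer analysis that drops its worst outcomes and so flatters DCS. The documents do not support that.
- Nothing says that data already collected are deleted or left out. Section 13.1 also states intention to treat, mixed models and multiple imputation. A completer-type analysis is one reading of an unresolved contradiction.
- Section 10 names enhanced fear learning as a potential danger. Worsening of OCD on the dosing days, the rule closest to that harm, leads to discontinuation only, as do serious adverse events. Section 11.8 keeps patients who worsen later. Declining a capsule or being lost is not necessarily a bad outcome.
- Section 5.3 speaks of the two dosing days, not of events after a capsule. The first capsule comes three hours into the Day 2 session.
- Section 13.2 does not say that losses at any time are replaced. Its next sentence can be read as plain over-enrolment. Section 11.7 ends the trial at 12 months and treats the 5-year data separately.
- Safety follow-up is not simply lost, given Sections 5.4 and 12.8.
- Suicidal ideation is an exclusion criterion at entry, and Section 13.1 reports no drop-outs so far from the intensive treatment.

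All of this stands, and it limits the size and direction of the problem. It does not remove the contradiction. An early end-of-study visit is not a 3- or 12-month outcome. Section 11.8 shows that the protocol can state retention when it means it, whereas Sections 5.3 and 11.7 state the opposite for their groups. The experience of no drop-outs concerns the four treatment days, not losses up to 12 months.

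**Conclusion.** The point holds as a contradiction in stated rules. Two groups of randomised patients are excluded and a third is replaced, while the analysis is declared intention to treat. If the rules are followed, the analysed set can differ from the randomised set, and T2 and T3 outcomes are missing for those excluded.

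The direction of bias is not determined. Under the assumptions set out above, with all 10 allowed drop-outs removed, d changes by +0.07 to +0.14 (all from DCS), −0.24 to −0.48 (all from placebo) or not at all (removals in proportion to allocation). The one-arm cases are extremes. If drop-out is as low as the protocol expects from the intensive treatment, the effect would be small. The conclusion about the contradiction rests on the text alone and needs none of these assumptions.

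**What to change.** Reconcile Sections 5, 5.3, 5.4, 11.7, 13.1 and 13.2. The change concerns follow-up, analysis set and replacement only; every clinical stopping rule stays as it is.
- **13.1:** state that all randomised patients are analysed in the arm assigned. A set limited to patients who took at least one capsule may serve as a sensitivity analysis.
- **5.3 and 11.7:** state that exclusion or discontinuation ends study treatment as those sections already specify, and that T1 to T3 and safety assessments continue unless the patient withdraws consent to follow-up. Align 5.4 with this, so that the end-of-study visit does not stand in for T2 and T3.
- **13.2 and 5:** delete the replacement of drop-outs, treat the 10 extra patients as up-front inflation, and reconcile the resulting 170 with the maximum of 160.

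The cost is protocol wording, a few assessments that are already scheduled, and possibly a slightly diluted effect estimate.

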#### ***Other possible reasons for premature discontinuation of treatment***

- Any serious adverse event or circumstances during the two days DCS administration justifying the discontinuation of the treatment in the investigator's opinion, if the serious adverse event is considered to be uniquely caused by DCS/placebo.
- Protocol deviation which jeopardizes the patient's safety.
- Patient lost to follow-up: When the participant discontinues reporting to the investigator, he/she must make an effort to contact the participant to establish the reason for discontinuation, and to suggest the participant comes to an end-of-study visit. If all such attempts to contact the participant fails, the investigator then declare the participant "lost to post-treatment assessment" and the investigator should document all these attempts in the corresponding medical file.

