### **5.4 Subject Log**

If possible, the investigator must record the reason and the exact time of the premature discontinuation of treatment in the case report form (CRF). If more than one reason is given, the investigator must indicate the main reason.

In case of treatment discontinuation for any reason between visits T0 and T2, an end-of-study visit should be done with all the assessments planned for the follow up as early as possible after the treatment study discontinuation.

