### **9.6 Treatment**

- **Day 1 Psycho-education and treatment preparation (3 h)**

Participants receive psychoeducation focused on the rationale behind the cET treatment which emphasizes the differences between this approach and the ERP they previously have received. Relevant exposure tasks will be decided upon. The patients are introduced to the micro-intervention “Leaning into the anxiety” (LET), which is to be practiced throughout the two days of exposure

- **Day 2 (8 hrs) and 3(8 h + 2 h psychoeducation for family): Therapist assisted Exposure and response prevention combined with DCS/ placebo**

Patients will engage in individually tailored and therapist assisted ERP, using the micro-intervention LET. Exposures will be conducted in a variety of settings with high ecological relevance, most of them out of the office. DCS on day 2 (first day of exposure) will be taken after 3 hours of the cET. DCS on day 3 will be given approximately 1 hour before the first exposure session of the day.

On day 3 the patient’s family/ significant others are invited to a 2 h psychoeducation.

- **Day 4: Summarizing and relapse prevention**

Summarizing (“lessons learnt”) and planning self-exposures for the next three weeks. Focus will be on teaching the patients how to be “their own therapists. The patients are provided with written information covering procedures and times for upcoming assessments. The patients will, in a group setting, give structured feedback/ evaluation of the treatment at the end, and will prepare exposure tasks to be performed the first three weeks after the treatment.

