## 11. Measures to minimize bias

The following procedures have been taken to avoid bias:

- This is a double-blind study and the study capsules will be of identical appearance in order to protect the blinding for both participants, therapists, assessors and investigators. As there are no obvious side effects associated with the drug, the placebo capsules will be passive.
- Post-treatment assessments of primary outcomes are conducted by specially trained assessors who are blinded to the treatment conditions and not involved in the treatment (see section 8.4).

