### **12.2 Definition of Adverse Reactions**

Each AE is to be classified by the investigator as related or not related to the IMP. An Adverse Reaction (AR) is a noxious and unintended medical *response* to a medical product related to any dose. For an AE to be an AR the suspected association between the product and the unwanted medical condition should be at least a reasonable *possibility*.

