### **12.4 Definition of Suspected Unexpected Serious Adverse Reactions**

Protocol No: 2013-002574-49

Date 09 September.2015

Version: 03

Each SAE that is at least possibly related to IMP is to be classified by the investigator as expected or unexpected. A SAE that is at least possibly related to IMP, and **unexpected**, is defined as a Suspected Unexpected Serious Adverse Reaction (SUSAR). It is expected if it is already known from earlier trials or is mentioned in relevant documents. The reference security information of the IMP can be found in the approved SPC (122).

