### **12.5.2 Assessment of Causality**

**Unlikely:** The event is most likely related to an etiology other than the IMP.

**Possible:** A causal relationship is conceivable and cannot be dismissed.

**Probably:** Good reason and sufficient documentation to assume a causal relationship.

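### Section 5.3 lists a serious adverse event on the dosing days as a reason to stop treatment only on the added condition that the capsule is its sole cause, a stricter test than any other causality threshold in the protocol

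*Protocol*

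**What the plan says.** Section 5.3 of the protocol has two lists. The mandatory list covers withdrawal of consent, high suicide risk or a suicide attempt on the dosing days, and worsening of OCD that in the investigator's opinion "requires an adaptation of treatment not compatible with the protocol or requires hospitalization". None of these carries a causality test.

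The second list gives other possible reasons. Its first bullet covers an SAE, or circumstances, on the two dosing days that the investigator believes justify stopping. The bullet ends with a further condition: "if the serious adverse event is considered to be uniquely caused by DCS/placebo".

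Causality is also addressed in four other places:
- Section 12.2, on adverse reactions: "For an AE to be an AR the suspected association between the product and the unwanted medical condition should be at least a reasonable" possibility.
- Section 12.4, on unexpected serious reactions: "Each SAE that is at least possibly related to IMP is to be classified by the investigator as expected or unexpected".
- Section 12.5.2, the rating scale, has three levels: *Unlikely*, *Possible* and *Probably*. The middle level reads "A causal relationship is conceivable and cannot be dismissed". The top level asks for good reason and adequate documentation to assume a causal link.
- Section 11.9 stops the whole study when serious side effects related to DCS are clearly documented in two or more patients.

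Under sections 8.6 and 9.6 the first capsule is taken three hours into the exposure session on Day 2, and the second about one hour before exposure starts on Day 3.

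**The concern.** The bullet asks two questions in sequence. The first is whether the event justifies stopping, in the investigator's opinion. The second is whether the capsule alone caused it. A patient whose SAE passes the first question and fails the second is not covered by the only criterion in section 5.3 that names an SAE.

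What is at stake is one practical decision: whether to give the second capsule, roughly a day after the first, to a patient who has just had an SAE. The written rule for that decision should not be narrower than the clinical judgement it is meant to support. Here it is.

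**Working it through.** No arithmetic applies. The check sets the causality standards side by side.

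| Section | What it governs | Causal standard |
|---|---|---|
| 5.3, mandatory list | Stopping one patient's treatment | None |
| 5.3, SAE bullet | Stopping one patient's treatment | Capsule is the sole cause |
| 11.9 | Stopping the study | Related to DCS, clearly documented, two or more patients |
| 12.2 | Classing an event as an adverse reaction | Reasonable possibility |
| 12.4 | Classing an SAE as expected or unexpected | At least possibly related |
| 12.5.2 | Rating each event | *Unlikely*, *Possible*, *Probably* |

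**Step 1: is the test found elsewhere?** No. The sole-cause condition occurs only in the SAE bullet of section 5.3. Sections 11.9, 12.2 and 12.4 all ask for a relation to the product, never for the absence of other causes. Section 11.9 does demand clear documentation and at least two patients, but its causal requirement is still only relatedness.

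**Step 2: can the rating scale answer it?** No. *Unlikely* points to another cause. *Possible* and *Probably* both satisfy the at-least-possibly-related standard of section 12.4. Neither excludes a contributing cause, so a rating of *Probably* does not by itself meet the condition in section 5.3.

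**Step 3: which events are affected?** Remove those that the mandatory list already covers: suicidality, and OCD worsening that needs hospitalization or treatment incompatible with the protocol. What remains is any other event meeting a seriousness criterion in section 12.3. As an illustration of mine, not one the protocol predicts, take a seizure after the first capsule that leads to admission. The investigator thinks treatment should stop and rates the relation *Possible*. The event is outside the mandatory list. Read literally, the SAE bullet does not cover it either.

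**Step 4: does anything compel a second capsule?** No. The second list is headed as possible reasons. Section 5.4 begins its instruction on the end-of-study visit with "In case of treatment discontinuation for any reason between visits T0 and T2", so it contemplates stopping on grounds that are not itemised. No text requires the second capsule after an SAE.

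The gap is therefore in the written criterion, and not in the investigator's freedom to act.

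**The case against.** The strongest reply is that the wording changes no decision. The list is open and permissive. The causal clause names only the SAE, so an investigator may be able to use the alternative of circumstances with no causality test at all. Patients can withdraw consent, and the mandatory list already captures suicidality and serious OCD worsening. All of this stands, and it is why the point is minor. It does not make the clause harmless: the one criterion written for SAEs still says something narrower than intended practice is likely to be.

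A reader might infer more than the document supports, in three ways.

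- **That the protocol forbids stopping, or forces the second capsule.** It does neither, for the reasons in step 4.
- **That sections 5.3 and 12 give contradictory rules for one decision.** Sections 12.2, 12.4 and 12.5.2 serve classification and reporting. Section 5.3 does not refer to the rating scale and need not map onto it. The comparison shows that the test is out of line with the rest of the protocol, not that two rules collide.
- **That blinding makes the test unworkable.** Section 11 does say "This is a double-blind study and the study capsules will be of identical appearance". But the condition asks about the capsule, active or placebo, and so does not require knowledge of the arm. Any causality rating in this trial is made under the same blinding and during the same long exposure sessions (section 9.6: "Day 2 (8 hrs) and 3(8 h + 2 h psychoeducation for family"). Section 11.3 also allows the code to be broken in life-threatening emergencies.

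The wording may also be loose English for *specifically caused*, meant to separate drug effects from distress due to exposure. That cannot be excluded. If so, the text still needs correcting, since a site will read what is written.

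**Conclusion.** The point holds as a minor defect in a stated safety rule. The rule is written out and badly fixed, so this is not detail left for another document. On a literal reading, the SAE bullet in section 5.3 leaves out SAEs beyond the mandatory list that the investigator already thinks justify stopping, unless the capsule is judged to be the only cause. That is stricter than the causal standard in sections 11.9, 12.2 and 12.4 and is not a level of the scale in section 12.5.2.

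The size cannot be expressed as a number of patients, because the protocol states no expected SAE rate. Counting how many bullets in section 5.3 mention an SAE would not measure it either, since that counts words and not coverage. There is no effect on power, error rates or the endpoint.

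The conclusion assumes that *uniquely* is read in its ordinary sense. The gap is narrower still if circumstances are taken to be free of the condition, which the text permits but does not settle.

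**What to change.** Delete the final condition of the SAE bullet in section 5.3, that is, the words "if the serious adverse event is considered to be uniquely caused by DCS/placebo". Any SAE on the dosing days that the investigator judges to justify stopping would then qualify. This is cleaner than lowering the causal threshold: once the investigator believes that stopping is justified, a causality gate adds nothing, and even a weaker one would exclude an event rated *Unlikely* that still warrants stopping.

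If the sponsor wants to keep a causal condition, use *at least possibly related to DCS/placebo (section 12.5.2)*, so that it rests on a rating the investigator already makes. In either case keep the bullet permissive and leave the decision on the second capsule with the investigator.

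The cost is one phrase and no new procedure. The small downside is that a few more patients may miss the second capsule.
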